## 1. Summary

The purpose of this study is to longitudinally assess the morphological and functional changes of inner ear in patients with active Ménière's disease (MD) between medications-alone group and positive pressure therapy (PPT) combined group by using inner ear gadolinium (Gd)-enhanced MRI and neuro-otological testings.

## 2. Background and Rationale

Ménière's disease (MD) is clinically characterized by recurrent vertigo, fluctuating hearing loss and persistent tinnitus with a high lifetime prevalence especially in middle-aged. Medical managements such as lifestyle modifications and medications are the first-line therapy, but twenty percent of MD patients are refractory to medical therapy and suffer frequent vertigo attacks with progressive profound hearing loss.

For intractable MD patients, available options other than function-ablative procedures are pressure pulse treatment (PPT) or endolymphatic sac surgery. MD is pathologically defined as the idiopathic endolymphatic hydrops (EH) in the inner ear and reducing EH is an hypothesized pathway in these two therapies; however, this has not been directly demonstrated for PPT. PPT using portable device is now a second-line therapy for intractable MD and a newly developed device was approved by Japan's public medical insurance system in September 2018.

EH, an objective index of treatment effect, is currently easily visualized using 3-Tesla magnetic resonance imaging (MRI) after intravenous administration of gadolinium (Gd). Using this imaging method, we characterized the morphology of *in vivo* EH in MD patients and measured EH volume semi-quantitatively. However, the hypothetical morphological changes of *in vivo* EH during PPT, i.e. the reduction of EH, has not yet to be well investigated.

## 3. Assessment and management of risk

### 3-1 Potential risk

1. Allergic reactions to MRI contrast agent
2. Transient nausea, vomiting, and worsening of vertigo at caloric testing.

### 3-2 Risk Management

Participants with asthma and kidney disease will be excluded from the study. Participants may be withdrawn from the study if they have prior reaction to contrast media.

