### **6-3 Study Duration**

Each participant will prescribe an osmotic diuretic at daily doses of 63 mg and receive audiometry once a month, video head impulse testing (vHIT) every 4 months, and caloric testing and MRI every 8 months for the duration of 36 months and will be followed up.

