### **7-3 Participant Exclusion Criteria**

Participants were also excluded from the study if a or more of the following criteria are met:

1. Participants had bronchial asthma or renal impairment.
2. Participants met the diagnostic criteria for vestibular migraine.
3. Participants had eardrum perforation or ear canal injury in the affected ear.
4. Pregnant or breastfeeding.
5. Any clinically significant or unstable medical or surgical condition that in the opinion of the PI or PI-delegated clinician may put the participant at risk when participating in the study or may influence the results of the study or affect the participant's ability to take part in the study as determined by medical history, physical examinations, or laboratory tests.

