### **7-4 Participant Stopping Criteria**

- 1) Participants withdrawal of consent
- 2) Non-compliance with the protocol
- 3) Occurrence of change in medical status or an incidental finding that leads the investigator concerned about the participant's welfare
- 4) Inability to continue, loss to follow-up
- 5) The termination of the study by the Chief/Principal Investigator (CI/PI).

If enrolled participants prematurely discontinue the study or do not comply with the protocol, additional participants may be enrolled as replacement participants and assigned to the same treatment sequence at the discretion of the Principal Investigator.

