## 8. Trial Procedures

All participants underwent neuro-otological testing and Gd-enhanced inner ear MRI within 2 weeks following their first consultation at our institution. Participants were instructed to record the date, time, severity, and duration of vertigo attacks in a self-reporting diary. We asked all participants to decide by the next consultation date in 2 weeks whether to receive PPT in addition to medications. The allocation to the additional PPT intervention was made by self-determination, and participants were then assigned to either the Control group or the PPT group, prescribed an osmotic diuretic at daily doses of 63 mg, and then followed.

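### A prior contrast-media reaction is only an optional, untimed ground for withdrawal, so no mandatory rule bars gadolinium after a known gadolinium hypersensitivity reaction

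*Protocol*

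**What the plan says.** Section 3-1 of the protocol lists two potential risks, and the first is "Allergic reactions to MRI contrast agent". Section 3-2, on managing those risks, deals with three conditions at two strengths. Asthma and kidney disease *will* lead to exclusion. For contrast history the text is "Participants may be withdrawn from the study if they have prior reaction to contrast media".

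Section 7-3 carries the first two conditions into the exclusion list as item 1: "Participants had bronchial asthma or renal impairment". None of its five items names a contrast reaction. Item 5 is a general clause for a medical condition "that in the opinion of the PI or PI-delegated clinician may put the participant at risk when participating in the study", and it cites medical history as one source for that opinion. In section 7-4, the closest stopping criterion is item 3: "Occurrence of change in medical status or an incidental finding that leads the investigator concerned about" the participant's welfare.

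On dosing, section 8 states: "All participants underwent neuro-otological testing and Gd-enhanced inner ear MRI within 2 weeks following their first consultation". Section 6-3 sets "caloric testing and MRI every 8 months for the duration of 36 months".

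**The concern.** Of the three conditions in 3-2, the contrast reaction is the one tied most directly to the risk listed in 3-1, yet it has the weakest rule. The word *may* leaves the action optional even when the history is known. *Withdrawn* suits someone already in the study, and no checkpoint places the decision before the first injection. Sections 8, 8-1, 8-2 and 9 describe no check of contrast history before the baseline scan.

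What is at stake is the safety of a participant who is known to have reacted to gadolinium, or who reacts at a study scan. The protocol can be followed to the letter and such a person can still be given the agent. Sample size, error rates and the planned comparison are not affected.

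**Working it through.** The protocol gives no figure to reproduce, so the check sets the rules side by side and asks of each whether it obliges anyone to withhold gadolinium.

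| Rule | Names a contrast reaction? | Usable before the baseline MRI? | Does it bar gadolinium? |
|---|---|---|---|
| 3-2, contrast sentence | Yes | Yes, as no earliest time is set | No; the action itself is optional |
| 7-3 item 1 | No | Yes | Only if the person also has asthma or renal impairment |
| 7-3 item 5 | No | Yes, through medical history | Only if the clinician judges that there is a risk; exclusion then follows |
| 7-4 item 3 | No | Fits poorly with a pre-existing history | Only if the investigator is concerned |
| 8-2, consent | No; hazards in general are explained | Yes | No; it is not an eligibility rule |
| 10-1 and 10-2 | Covers it as an adverse event | No; it applies after an event | No; it requires action, recording and reporting |

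**Two readings of a prior reaction in 3-2**

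- *A reaction before the study.* Section 3-2 then names the right condition but only permits action. The other route before baseline is 7-3 item 5, which turns on an opinion.
- *A reaction at an earlier study scan.* Section 3-2 then names that event, again only as a permission, and pre-study history is left to 7-3 item 5.

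On either reading, no rule makes withholding gadolinium mandatory.

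**Count of conditions in 3-2**

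- Conditions named: 3.
- Mandatory and carried into 7-3: 2 (asthma, kidney disease).
- Optional and not named in 7-3: 3 − 2 = 1 (contrast reaction).

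**Scheduled scans**

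- Section 9 table: first consultation and 8 months = 2.
- Section 6-3, every 8 months for 36 months: 1 + floor(36/8) = 1 + 4 = 5 (months 0, 8, 16, 24, 32).
- Still scheduled after a reaction at the baseline scan: 2 − 1 = 1 under the table, or 5 − 1 = 4 over 36 months.

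Only the baseline scan is expressly called Gd-enhanced in the procedures. That the repeat scans also use gadolinium is an assumption. It is supported by section 1, where the longitudinal comparison is made "by using inner ear gadolinium (Gd)-enhanced MRI and neuro-otological testings".

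**The case against.** The strongest reply is that working safeguards exist. Section 3-2 names this very ground and, being untimed, can be used before the baseline scan. It is operative text, and its absence from 7-3 does not cancel it. Item 5 of 7-3 is firmer than 3-2: opinion decides whether there is a risk, but once a risk is found the lead-in to 7-3 makes exclusion follow. For a reaction during the study, section 10 requires immediate action, an entry in the case report form and an immediate report to a supervisor and the CI/PI. The decision therefore reaches someone able to stop further scans. For a known reactor to be scanned, a clinician would have to decline to use 3-2 and also find no risk under item 5.

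All of this stands, and it rules out two stronger readings. A reader might infer that nothing mandatory in the protocol touches a contrast reaction. Section 10 shows otherwise, although none of its duties withholds the next dose. A reader might also infer that 3-2 and 7-3 contradict each other. They do not: they agree on asthma and renal disease, and 7-3 is merely silent on the third condition.

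There is also a fair reason for *may*. Section 3-2 speaks of contrast media in general and of reactions of any kind. A mandatory rule on those words would remove people with mild, non-allergic or unrelated reactions. That argues for a narrow rule on gadolinium hypersensitivity. It does not justify leaving that narrower case optional when asthma and renal impairment were not.

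**Conclusion.** The point holds as a weakness in a stated safety rule. The protocol identifies contrast allergy as a risk, and no mandatory rule bars gadolinium for a participant with known gadolinium hypersensitivity at the baseline MRI, or after such a reaction during the study.

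Its size is limited. The number of participants concerned cannot be derived from the protocol and may be zero. A reader might take the 2 to 5 scheduled scans as the doses that an affected participant would receive. The documents do not support that: these are schedule counts, the upper figure assumes that repeat MRIs use gadolinium, and a clinician could stop dosing before any of them. Nor should the point be read as a flaw in the analysis, since the ground is patient safety only. The change should be made because it is specific, safer and nearly free.

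**What to change.** - **7-3:** add an exclusion for *prior hypersensitivity reaction to gadolinium-based contrast media*, to be checked before the baseline MRI.
- **7-4:** state that no further gadolinium is given after a hypersensitivity reaction to study contrast.
- **3-2:** align the sentence on contrast reactions with both rules.
- **Left as it is:** reactions to other contrast media, and non-allergic reactions, stay with clinician judgement, with 7-3 item 5 as the route at entry.

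The cost is one line in each of 7-3 and 7-4, a matching edit to 3-2 and one screening question. Under section 15, a change to the plan needs prior ethics committee approval. The downside is a very small loss of eligible patients or of follow-up MRI data. Section 7-4 already allows replacement of participants who discontinue early.

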## 4. Objectives

### 4-1 Primary Objectives

To assess the change of EH volume.

### 4-2 Secondary Objectives

To assess the frequency of vertigo attacks per months using self-reporting diary.

To assess hearing function by PTA thresholds once a month.

To assess vestibular function by max-SPEV and VOR gain every 4 months.

## 5. Trial Design

This is a single-centre, prospective, nonrandomized-controlled, clinical trial with two arms: a control group, which were prescribed an osmotic diuretic and betahistine mesilate, and a treatment group, which self-selected to use a PPT device in addition to the same medications.

## **6. Study Settings**

### **6-1 Site Selection**

This study will be conducted at Kansai Rosai Hospital (KRH).

### **6-2 Study Setting**

All participants assessments will be performed at KRH.

### **6-3 Study Duration**

Each participant will prescribe an osmotic diuretic at daily doses of 63 mg and receive audiometry once a month, video head impulse testing (vHIT) every 4 months, and caloric testing and MRI every 8 months for the duration of 36 months and will be followed up.

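### The osmotic diuretic given to both arms is fixed at 63 mg a day, a dose too small to act osmotically, so the number, the unit or the drug class is wrong

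*Protocol*

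**What the plan says.** Three places in the protocol describe the background medication.

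- **Section 5 (Trial Design)** defines the comparator as "a control group, which were prescribed an osmotic diuretic and betahistine mesilate". The other arm is the one "which self-selected to use a PPT device in addition to the same medications". No dose is given here for either drug.
- **Section 6-3 (Study Duration)** gives the dose: "Each participant will prescribe an osmotic diuretic at daily doses of 63 mg". The same sentence lists the tests and sets the schedule "for the duration of 36 months and will be followed up".
- **Section 8 (Trial Procedures)** repeats it in a separately worded sentence. After the patients' own choice of treatment, "participants were then assigned to either the Control group or the PPT group", and were "prescribed an osmotic diuretic at daily doses of 63 mg, and then followed".

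No section names the osmotic agent, gives a volume or concentration, or states the dose in another unit. The 63 mg figure is the only drug dose in the protocol.

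**The concern.** Osmotic diuretics are defined by mechanism: they add enough solute to hold or draw water. That takes gram quantities of a small molecule, and a dose in the tens of milligrams belongs to drugs that act on a receptor or transporter. The stated class and the stated quantity therefore do not fit together.

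What is at stake is the definition of the treatment. The control arm consists of two drugs, and this is one of them. The trial asks what PPT adds to that background over a 36-month schedule. If the text were followed literally, both arms would receive an osmotically inert dose, and PPT would not be tested on top of the therapy that section 5 describes. If clinicians prescribe something else, the written protocol does not record what it was. In either case a reader cannot tell what PPT was added to and cannot repeat the regimen.

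**Working it through.** The protocol gives no derivation or source for the dose, so there is no figure of its own to reproduce. The check is whether the stated amount could do what the stated class requires.

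**Input from the protocol:** 63 mg a day, class osmotic diuretic, both arms (sections 5, 6-3 and 8).

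**Assumptions, not in the protocol:** solute of 60 to 182 g/mol, contributing one osmole per mole; plasma osmolality 290 mOsm/L; extracellular fluid 14 L; total body water 30 to 45 L; daily urinary solute 600 to 900 mOsm.

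**Step 1. Osmotic load = dose / molecular weight.**
- 63 mg / 182 g/mol = 0.346 mOsm
- 63 mg / 60 g/mol = 1.05 mOsm

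**Step 2. Water held = load / plasma osmolality.**
- 0.346 / 290 = 0.00119 L = 1.2 mL
- 1.05 / 290 = 0.00362 L = 3.6 mL

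Using 300 instead of 290 mOsm/L gives 1.15 to 3.5 mL.

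**Step 3. Rise in osmolality = load / fluid volume.**
- Extracellular fluid: 0.346 / 14 = 0.025 and 1.05 / 14 = 0.075 mOsm/L
- Total body water: 0.346 / 45 = 0.008 and 1.05 / 30 = 0.035 mOsm/L

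The largest of these, 0.075 mOsm/L, is 0.075 / 290 = 0.026% of plasma osmolality.

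**Step 4. Share of daily urinary solute.**
- 0.346 / 900 = 0.04%
- 1.05 / 600 = 0.18%

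**Step 5. The same steps at 63 g**, for scale only:

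| Quantity | 63 mg | 63 g |
|---|---|---|
| Load (mOsm/day) | 0.35 to 1.05 | 346 to 1050 |
| Water held | 1.2 to 3.6 mL | 1.2 to 3.6 L |
| Rise in body-water osmolality (mOsm/L) | 0.008 to 0.035 | 7.7 to 35 |
| Share of urinary solute | 0.04% to 0.18% | 38% to 175% |

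**Step 6. Does the result depend on the assumed solute?** Two extremes outside the range:
- At 18 g/mol, the weight of water itself and lighter than any realistic agent: 63 / 18 = 3.5 mOsm, and 3.5 / 290 = 12 mL.
- At 60 g/mol with two particles per molecule: 2 × 1.05 = 2.1 mOsm, and 2.1 / 290 = 7 mL.

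Both remain negligible. An agent heavier than 182 g/mol gives a smaller load than the lower limit above.

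**The case against.** The best counter-argument is that the protocol does not contradict itself. Sections 5, 6-3 and 8 agree on the class, and sections 6-3 and 8 agree on the dose. The mismatch appears only when general physiology is brought in. That is true, and it is why the assumptions are listed. The conclusion does not turn on their exact values, because the load is negligible across the whole range and at the extremes beyond it.

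A second objection is practical. This is one hospital, patients are approached by their treating clinicians in routine care, and no drug is named, so nobody could dispense from this text alone. Nothing shows that any patient was given 63 mg of an osmotic agent. This stands, and no claim of actual underdosing is made here. It does not excuse the text: if clinicians rely on their own knowledge of the right dose, the protocol misstates the treatment for every participant.

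A third objection is that mg for g is only one candidate. A volume unit for a liquid product, a wrong number or a wrong class label would also explain the mismatch. This stands too. The 63 g column shows that a unit slip would be sufficient, not that it happened.

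Finally, the inference is untouched, since both arms share the medication, and the regimen is incompletely described anyway because betahistine has no stated dose. Both points are fair and limit the severity. They do not make the stated dose correct.

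**Conclusion.** The concern holds. An osmotic diuretic at 63 mg a day delivers 0.35 to 1.05 mOsm and holds about 1 to 4 mL of water, so class and quantity cannot both be right. This rests on a solute of 60 to 182 g/mol and ordinary values for plasma osmolality, fluid volumes and urinary solute. No realistic solute changes the conclusion. The same number and unit stand in two independently worded sentences, so a text-reading fault is unlikely.

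The protocol does not show whether the number, the unit or the class is the slip; if the class label is wrong, 63 mg could stand. The error is common to both arms and does not bias the group contrast. It damages the definition and reproducibility of the background therapy, and it should be corrected.

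**What to change.** Name the osmotic agent, and correct its dose and unit together in sections 6-3 and 8 against the product actually prescribed. If the agent turns out not to be an osmotic diuretic, correct the class in sections 5, 6-3 and 8 instead. The right dose cannot be read from the protocol and has to come from the prescribing record. Adding the betahistine dose in the same amendment would make the regimen repeatable.

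The cost is a wording change in two sections, or three if the class is wrong, with the ethics committee approval that section 15 requires. Visits, sample size and analysis stay as they are.

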## **7. Eligibility Criteria**

### **7-1 Study population**

Participants were required to be diagnosed as unilateral definitive MD according to the criteria of the AAO-HNS, with repeat definitive vertigo attacks of more than one per month for the 2 months prior to entering the study despite diet and lifestyle modifications. An additional entry criterion was a functionality level of 3 to 4. Fifty participants will be enrolled into the study.

### **7-2 Participant Inclusion Criteria**

- 1) Male or female
- 2) No age limits
- 2) Confirmed diagnosis of Ménière's disease at any time; according to the 1995 criteria of AAO-HNS.

### **7-3 Participant Exclusion Criteria**

Participants were also excluded from the study if a or more of the following criteria are met:

1. Participants had bronchial asthma or renal impairment.
2. Participants met the diagnostic criteria for vestibular migraine.
3. Participants had eardrum perforation or ear canal injury in the affected ear.
4. Pregnant or breastfeeding.
5. Any clinically significant or unstable medical or surgical condition that in the opinion of the PI or PI-delegated clinician may put the participant at risk when participating in the study or may influence the results of the study or affect the participant's ability to take part in the study as determined by medical history, physical examinations, or laboratory tests.

### **7-4 Participant Stopping Criteria**

- 1) Participants withdrawal of consent
- 2) Non-compliance with the protocol
- 3) Occurrence of change in medical status or an incidental finding that leads the investigator concerned about the participant's welfare
- 4) Inability to continue, loss to follow-up
- 5) The termination of the study by the Chief/Principal Investigator (CI/PI).

If enrolled participants prematurely discontinue the study or do not comply with the protocol, additional participants may be enrolled as replacement participants and assigned to the same treatment sequence at the discretion of the Principal Investigator.

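### The rule for replacing stopped participants conflicts with self-chosen treatment and selects the followed groups on events after that choice; the direction of any resulting bias cannot be read from the protocol

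*Protocol*

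**What the plan says.** Protocol section 7-4 lists "Non-compliance with the protocol" and "Inability to continue, loss to follow-up" among the criteria for stopping a participant. It then gives a replacement rule. The trigger is "If enrolled participants prematurely discontinue the study or do not comply with the protocol", and the consequence is that "additional participants may be enrolled as replacement participants and assigned to the same treatment sequence at the discretion of the Principal Investigator".

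The design is described in section 5 as a "single-centre, prospective, nonrandomized-controlled, clinical trial with two arms", with "a treatment group, which self-selected to use a PPT device in addition to the same medications". Section 8 repeats the mechanism: "The allocation to the additional PPT intervention was made by self-determination". That choice is made by the consultation two weeks after the first.

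Section 7-1 gives the size: "Fifty participants will be enrolled into the study". It gives no split by arm and does not say whether replacements fall within the fifty or come on top. Section 6-3 sets follow-up at 36 months. Section 8-1 notes that the treating clinician may also be the Principal Investigator.

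**The concern.** Two things look wrong.

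First, the replacement rule presupposes that someone other than the participant decides the arm. It also speaks of a treatment sequence, which a parallel two-arm design does not have. Taken literally, it means either overriding a new participant's choice or enrolling people according to the arm they intend to choose.

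Second, stopping and replacement depend on events after the treatment choice, and the only stated criterion for replacing is the Principal Investigator's discretion. That person may be the treating clinician and may know both the arm and the clinical course; the protocol describes no masking. If those who stop have worse (or better) outcomes than those who stay, and their later outcomes are not collected, the groups compared are no longer those who made the choice. This adds a second selection step to a comparison already exposed to confounding by self-selection. A larger sample does not remove it. Nor can an analysis plan written later recover assessments that were never made.

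**Working it through.** **Step 1: set the sections side by side.**
- Sections 5 and 8: the arm follows from the participant's own decision.
- Section 7-4: the replacement's arm follows from the arm of the person replaced.

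Both can hold only if the replacement happens to choose the vacated arm. Section 8 does say that participants were assigned to a group, but only after their own decision, so it does not reconcile the two.

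**Step 2: what the protocol supplies for sizing.** It gives fifty participants in total. It gives no stopping rates, no outcome SD and no allocation ratio. The sample size section gives no alpha, power or effect, so the figure of fifty cannot be reproduced. Everything below is illustration under stated assumptions.

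**Step 3: assumed model.** No true effect; outcome Y standard normal, lower is better; 25 per arm. In each arm a fraction d stops, when a latent score with correlation ρ to Y exceeds its (1 − d) quantile. Only completers and completing replacements are compared. Then

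E[Y | stays] = −ρ · φ(z₁₋d) / (1 − d),

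and the bias is the PPT value minus the control value (negative favours PPT).

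Values of φ(z₁₋d)/(1 − d):
- d = 5%: 0.1031/0.95 = 0.109
- d = 10%: 0.1755/0.90 = 0.195
- d = 20%: 0.2800/0.80 = 0.350
- d = 30%: 0.3477/0.70 = 0.497

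Example, ρ = 0.5, stopping 30% in PPT and 10% in control: −0.5 × (0.497 − 0.195) = −0.151 SD.

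| Stopping, PPT / control | ρ = 0.3 | ρ = 0.5 | ρ = 0.7 |
|---|---|---|---|
| 20% / 5% | −0.072 | −0.121 | −0.169 |
| 30% / 10% | −0.091 | −0.151 | −0.211 |
| 20% / 20% | 0 | 0 | 0 |
| 5% / 20% | +0.072 | +0.121 | +0.169 |
| 10% / 30% | +0.091 | +0.151 | +0.211 |

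With ρ = 0 the bias is zero in every row.

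**Step 4: effect on the test.** SE = √(2/25) = 0.283. The chance of a false result in favour of PPT is Φ(−1.96 − bias/SE). For bias −0.151 this is Φ(−1.96 + 0.534) = 7.7%, against 2.5% with no bias. The mirrored rates give the same 7.7% in favour of control.

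**Step 5: extreme case.** Exactly the worst 20% of PPT outcomes stop (ρ = 1) and no control stops: bias 0.350 SD in favour of PPT. In 20,000 simulated trials, the nominal two-sided 5% test rejected 27% of the time. With 20% stopping in both arms at ρ = 1, the bias is 0 and the rejection rate 5%.

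**Step 6: scale.** At two-sided 5% and 80% power (assumed), 25 per arm detect (1.960 + 0.842) × 0.283 = 0.79 SD. A bias of 0.07 to 0.21 SD is roughly a tenth to a quarter of that.

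**The case against.** A reader might infer that the rule biases the trial toward PPT. The reasoning would be that only PPT users have a device to abandon and that those without benefit abandon it. That is plausible, but the documents do not establish it. The rule is the same in both arms, and no stopping rates are given. Control participants enter with active vertigo, and the device is covered by public insurance according to section 2. Controls who do badly might therefore leave or take up the device, which would push the other way. A near-perfect link between stopping and outcome is also hard to believe for endolymphatic hydrops volume, which patients cannot feel and which is imaged every 8 months.

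A reader might also infer that stopped participants' data are discarded. Section 7-4 does not say so. In the model above the bias comes from leaving their outcomes out; replacement merely restores the number. Analysis sets may be settled in a statistical analysis plan that is not shown, and their absence from the protocol is not the point here. Replacement is optional as well, and the wording may be template text.

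These objections remove any claim about direction and any single headline figure. They do not remove the conflict between section 7-4 and sections 5 and 8, or the open-ended discretion. They also leave the follow-up problem: the section ends participation on post-choice events and makes no provision for assessing those people afterwards.

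**Conclusion.** The point holds in limited form. The conflict over how a replacement gets an arm needs no assumptions and must be reconciled. Selection on events after the treatment choice is a real route to bias, but its sign and size are not determined by the protocol. Bias toward PPT is a reasonable suspicion and no more. The illustrative range is zero under equal outcome-related stopping, about 0.07 to 0.21 SD either way for the unequal rates shown with correlations of 0.3 to 0.7, and 0.35 SD in a one-sided extreme. All of this rests on an assumed 25 per arm, no true effect, a normal outcome, and stopped participants' outcomes being left out. It should be fixed, but the evidence does not make it a fatal flaw.

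**What to change.** Amend one paragraph of section 7-4:

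- Delete the sentence that assigns replacements, or state that any later enrolees choose their own arm as in section 8 and do not displace earlier participants.
- For data collection, record non-compliance or stopping the device as an event rather than an end to follow-up. Continue the scheduled assessments in the group chosen at the 2-week visit, unless consent is withdrawn or the protocol's own provisions on participant welfare (section 7-4) or contrast reactions (section 3-2) apply. Those provisions stay as they are.
- State that all data collected before stopping remain in the main comparison by chosen group, and carry this into the statistical analysis plan. A compliers-only analysis can be supportive.

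The cost is a short amendment, which section 15 requires the ethics committees to approve in advance, and the effort of following people who have stopped. Including non-users will dilute the estimated effect somewhat.
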